### Moderators

#### Physiological assessments

The Empatica E4 wristband will be used to measure obtain physiological signals (see https://www.empatica.com/en-eu/research/e4/). Empatica offers physiological signals in raw data format (e.g., EDA, blood volume pulse, temperature and movement) or processed format (e.g., Heart rate and inter beat interval), and offers a visualization feature [34, 35]. *EDA* (i.e, skin conduction) from the Empatica E4 will be measured with dry electrodes that detect changes in the electrical conductivity of the skin. *HR* (i.e, Heart Rate) will be recorded with a photo plethysmography (PPG) sensor that emits green (i.e., light absorption is higher in oxygenated blood) and red light (i.e., to detect motion artifacts) and samples at a frequency of 64 Hz with which a blood volume pulse (BVP) signal is obtained [36, 37]. The resolution of the sensor output is 0.9nW per digit. PPG sensors are used to measure volume changes in the blood. The PPG sensor provides a signal that can be used to calculate HR, but can also be used to calculate other vital signs such as breathing rate and blood pressure [38]. The Empatica E4 also contains an optical infrared skin *temperature* sensor that samples at a frequency of 32 Hz and a resolution of 0.02 Celsius degrees. *Movement* with the Empatica E4 will be sampled at a frequency of 32 Hz (and has a resolution of 8 bits) with a sensor that measures acceleration in space over time on an x, y, and z-axis [39].

We will use an R package software called “Wearables” and an accompanying R Shiny application called “E4 dashboard”. This software can be used by clinicians and researchers to visualize and (batch) analyze physiological signals that are obtained with the Empatica E4. To our knowledge, this is the first R package with accompanying Shiny application that simultaneously processes physiological signal data, offers flexible signal pre-processing, artifact detection, feature extraction [40], and has a built-in visualization tool.

Both parents and their children will be instructed to wear the Empatica E4 on their nondominant hand during the experiment. Prior to the microtrial intervention, they will undergo a 5-minute resting baseline session, which is a common procedure to achieve a measurement of baseline recordings to which to compare the parameters retrieved during the experiment.

### Primary outcomes

#### Parental self-efficacy beliefs

Parents’ self-efficacy beliefs (SEBs) will be assessed with the General Scale of Parental Self-Efficacy Beliefs (GSPSEB) at pretest, posttest and follow-up [41]. This 25-item scale is related to five domain-specific SEB factors: Discipline, Nurturance, Playing, Instrumental Care, and Teaching. Self-efficacy beliefs in parenting can be evaluated as a quantitative construct by asking parents their beliefs in specific parenting activities, such as teaching, playing, providing instrumental care, nurturing or disciplining their child. Items are in the form of affirmatives, for example: ‘‘I am able to sense when my child is starting to become distressed” for the Nurturance subscale. The items will be rated on a 5-point scale (1 = strongly disagree to 5 = strongly agree).

#### Reported and observed parenting behavior

Reported parenting behavior will be assessed with the short version of the Parental Behavior Scale (PBS-S) at pretest, posttest and follow-up [42]. This questionnaire consists of 25 items and comprises five subscales: Positive parenting (e.g., “I make time to listen to my child, when he/she wants to tell me something”), Discipline (e.g., “When my child has been disobedient, I give him/her a chore as punishment”), Harsh Punishment (e.g., “I spank my child when he/she is disobedient or naughty”), Material Rewarding (e.g., “I give my child candy as a reward for good behavior”), and Rule Setting (e.g., “I teach my child to be polite at school”). A 5-point scale is provided for each item, ranging from 1 = (almost) never to 5 = (almost) always.

The Crowell Parent-Child interaction task procedure will be used to observe and rate parent behavior [43, 44]. Based on the Crowell procedure, the observation task takes 20 minutes to complete and consists of four episodes: warm-up, free play, frustration task, and recovery time. The parent scales are each internally consistent and well-defined conceptually. High internal consistency for each scale provides support for the reliability of the rating scale, and suggests that the Crowell scores can be useful as two separate scales measuring a child’s affective presentation and caregiver responsiveness, but also collectively as a total score assessing overall relational functioning (e.g., [45]).

### Secondary outcomes

#### Reported and observed child behavior

One subscale assessing the degree to which child externalizing problem is a problem from the 36-item Eyberg Child Behavior Inventory (ECBI) will be used at pretest, posttest and follow-up—to assess the occurrence of reported child externalizing problem behavior [46]. This “Intensity” subscale measures frequency of externalizing behavior in children aged 2 to 16 years and has been shown to be a reliable (screening) instrument [3]. Example items are: “Does not obey house rules” and “Whines.”

Child behavior will be observed using the same interaction paradigm used to observe parent behavior [43, 44]. The parent and child scales of the Crowell procedure are each internally consistent and well-defined conceptually. As previously mentioned, high internal consistency for each scale provides support for the reliability of the rating scale, and suggests that the Crowell scores can be useful as two separate scales measuring a child’s affective presentation and caregiver responsiveness (e.g., [45]).

### Discontinuation and withdrawal

All participants are allowed—and, in case needed, are assisted–to seek mental health care and parenting support through regular services. Also, enrolled participants can withdraw from the microtrial without further explanation at any point. There will be a debriefing at the end of the experiment, where they will be thanked for her/his participation and remunerated for their participation and travel expenses. We will offer participants the possibility to contact us (or a similar institution, counsellor, or experienced researcher for data collections outside Tilburg University) in case their participation in the study was in any case emotionally stressful and they feel like they need support or want to discuss this.

### Analyses

The data will be collected anonymously by assigning an ID number. Statistical analysis will involve several steps. First, using independent t-tests and/or alternative non-parametric tests, we will examine as a preliminary analysis whether randomization was successful, comparing baseline levels of demographics, parenting behavior and child externalizing behavior across the intervention and control condition. Possible significant differences at baseline will be used as covariates in analyses [47]. Latent change (LC) models in Mplus [48] will be used to test hypothesis H1-H3 on each dependent variable—parental self-efficacy beliefs, parenting behavior, child externalizing behavior and observed parenting and child behavior [49]. Because change is measured directly through latent difference variables, representing inter-individual differences in models are an excellent approach to examining repeated measures to estimate amount of change across time. In an LC model of parenting behavior and child behavior, behavioral change is cast as a latent variable, thereby separating measurement error. The mean of the latent difference variable is used as measure of mean differences between measurements, one to be predicted by other variables, including experimental condition (i.e., “micro” parenting intervention vs. control) and physiological scores. The Bonferroni correction is used to reduce chances of obtaining false-positive results (type I errors) [50].

### Hypothesis 1

◾ The feature of the LC model which evaluates this hypothesis links the “micro” parenting intervention (vs. control) with intervention responsiveness across pretest, posttest, and follow-up assessments, Specifically, the first model affords evaluation of group differences on the change from pretest to posttest and from posttest to follow-up. The second model affords evaluation of group differences from pretest to follow-up and from posttest to follow-up. Because the “micro” parenting intervention is focused on inducing parental self-efficacy beliefs, presumed to affect parents and children by changing their competence as a parent, we will also evaluate whether intervention effects are more pronounced when parents increase more rather than less in self-efficacy beliefs. We have four outcome measurements: reported and observed parenting change and reported and observed change in child behavior.

### Hypothesis 2

◾ The same LC approach will be employed here, as delineated in H1, with the “micro” parenting intervention once again serving as the predictor in a primary model, but this time adding parents’ physiological profile and its interaction with intervention—in which each moderator will be tested separately, in separate models.This model controls for the correlation between parents’ physiology and pretest parenting behavior. In a second phase of modeling, a composite moderator index of physiological assessments will be created, with the same being done with their children.

### Hypothesis 3

◾ The very same LC model, as delineated in H1 and H2 will be used, but this time to evaluate the predictive value of the interaction between “micro” parenting intervention, parents’ physiology, and child’s physiology on change in child behavior. This model controls for the correlation between parents’ physiology and pretest parent behavior, between child’s physiology and pretest child behavior, between parents’ physiology and child’s physiology, as well as prior levels of child behavior.

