### Recruitment

Based on previous work that demonstrated medium effects (*d*) of the “micro” parenting intervention [10, 11, 29, 30] and a priori power analyses for investigating our hypotheses in a two-sided test at α = .05 and power (1-β) = .80 [31], data will be collected from 120 four-to-six-year-old children and their parents—recruited via flyers, social networks and letters distributed by elementary schools in The Netherlands (Fig 1). Exclusion criteria for the children will be *(a)* psychiatric/neurological disorder (as reported by the parent), *(b)* mental retardation (IQ < 70), *(c)* not mastering the Dutch language, and *(d)* that their child is not living in another household during the weekdays. The sample will be recruited, and all data collection will be carried out by the Lifespan Lab of Developmental Psychology at Tilburg University.

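### Covariates are to be chosen by significance tests of baseline differences, and adjustment of change for the pretest score is stated only for Hypothesis 3

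*Protocol article*

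**What the plan says.** The Analyses section of the protocol article opens with t-tests or non-parametric tests: "we will examine as a preliminary analysis whether randomization was successful", by "comparing baseline levels of demographics, parenting behavior and child externalizing behavior across the intervention and control condition". It then fixes the consequence: "Possible significant differences at baseline will be used as covariates in analyses".

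The outcome models are latent change models in which condition and physiology predict change. "The mean of the latent difference variable is used as measure of mean differences between measurements".

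On the role of the pretest, the three hypotheses are described differently:

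- **Hypothesis 1:** "the first model affords evaluation of group differences on the change from pretest to posttest and from posttest to follow-up". A second model covers pretest to follow-up and, again, posttest to follow-up. No adjustment of change for pretest is mentioned.
- **Hypothesis 2:** "This model controls for the correlation between parents’ physiology and pretest parenting behavior". This is an association between moderator and pretest. It does not say that change is regressed on pretest.
- **Hypothesis 3:** the list of controls ends with "as well as prior levels of child behavior". This is the only stated control for the starting level of the outcome.

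**The concern.** Two things are at issue.

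First, the selection rule. If allocation is random and does not influence the pretest, every baseline difference is a chance difference. A p-value for it therefore carries no information about whether randomisation worked. Nor does it say whether the variable predicts the outcome, which is what makes a covariate useful. The rule lets in a weakly related variable that happens to cross .05 and leaves out a strongly prognostic one that does not. The fitted model is then decided by the data rather than in advance.

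Second, the pretest score of each outcome is normally its strongest single predictor, and the trial plans to measure it on everyone. If H1 and H2 compare change without conditioning on pretest, the comparison is less precise than it could be. It also carries regression to the mean whenever the arms happen to start apart. H1 and H2 cover the primary parenting outcomes, in a trial of 120 families with interaction hypotheses and a Bonferroni correction.

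**Working it through.** **1. The plan's own figure.** The Recruitment section gives 120 families "in a two-sided test at α = .05 and power (1-β) = .80" for a medium effect, without a number for medium. With n per arm = 2(1.960 + 0.842)²/d²:

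- d = 0.5 gives 15.70/0.25 = 62.8, so 63 per arm and 126 in total. Power with 60 per arm is 0.78.
- d = 0.512 gives 15.70/0.262 = 59.9, so 60 per arm and 120 in total.

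The figure can be neither strictly reproduced nor refuted, and nothing below depends on it. I use d = 0.5 only as an illustration.

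**2. What the rule selects.** With sound randomisation and tests at .05, a given pretest score that is tested enters in about 5% of trials. The article does not say how many tests will be run. If there were k independent tests (an assumption), the chance that at least one covariate enters is 1 − .95^k: 14% for k = 3, 23% for k = 5, 40% for k = 10. Correlated tests would change these figures. Self-efficacy beliefs are a primary outcome but are not among the variables listed for testing, so as written the rule could not bring in their pretest score.

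**3. What pretest adjustment is worth.** Assumptions: observed scores, SD 1 at both times, correlation r (not in the document), main effect of condition on pre-to-post change.

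- Variance of change: 2(1 − r)
- Variance after regression on pretest: 1 − r²
- Ratio: (1 − r²)/[2(1 − r)] = (1 + r)/2

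Power is for 60 per arm, and N is the total for 80% power. Both use the normal approximation with d = 0.5 on the score scale and two-sided α = .05, before any Bonferroni correction.

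| r | Var, change | Var, adjusted | Ratio | Power, change | Power, adjusted | N, change | N, adjusted |
|---|---|---|---|---|---|---|---|
| .3 | 1.40 | 0.91 | 0.65 | 0.64 | 0.82 | 176 | 116 |
| .5 | 1.00 | 0.75 | 0.75 | 0.78 | 0.89 | 126 | 96 |
| .7 | 0.60 | 0.51 | 0.85 | 0.94 | 0.97 | 76 | 66 |
| .8 | 0.40 | 0.36 | 0.90 | 0.991 | 0.995 | 52 | 46 |

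**4. Does the rule recover this gain?** Simulation of 40,000 trials per setting, 60 per arm, one outcome, with its pretest as the only candidate covariate. Test-then-adjust means that the pretest enters only if it differs significantly between arms. The last column is the type I error of unadjusted change in trials where the baseline gap exceeds 0.25 SD but is not significant.

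| r | Power, change | Power, test-then-adjust | Power, always adjust | Type I error, test-then-adjust | Type I error, unnoticed gap |
|---|---|---|---|---|---|
| .3 | 0.63 | 0.64 | 0.81 | 0.042 | 0.117 |
| .5 | 0.77 | 0.78 | 0.88 | 0.043 | 0.093 |
| .7 | 0.94 | 0.94 | 0.97 | 0.046 | 0.081 |
| .8 | 0.990 | 0.991 | 0.995 | 0.046 | 0.069 |

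The rule recovers almost none of the power. Its overall type I error is slightly below .05.

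**5. Why the last column is high.** Given a baseline difference Δ between arms, the expected difference in change under no effect is (r − 1)Δ. At Δ = 0.25 and r = .5 this is −0.125 SD, although the test has not flagged the gap.

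**The case against.** **The model may already contain the pretest.** A latent change model for pre-to-post change includes the pretest by construction. Regressing change on it, or holding pretest means equal across arms, would regain most of the precision. H3 is introduced as the same model as in H1 and H2, so its list of controls can be read as describing a common model. A journal article may leave the exact paths to the full protocol or analysis plan. This stands in part. A reader might infer that H1 and H2 do not adjust for pretest, but the article does not say that; it is silent. The silence does not rescue the selection rule, which is stated outright, and an analysis plan with a fixed covariate set would contradict it.

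**The size is not the trial's own.** No correlation is given, and at r = .8 the gain is small. The formula is for observed scores, whereas the plan separates measurement error; latent scores would have a higher r and so a smaller gain. It describes a main effect on pre-to-post change, not the H2 and H3 interactions or the posttest-to-follow-up change. All of this stands, so the gain is shown as a range.

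**Validity is not at risk overall.** Unadjusted change is unbiased over repeated randomisations, and the simulated type I error is 0.042 to 0.046. This stands. The error-control problem is conditional on an imbalance that is present but not significant.

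**Baseline differences might not be pure chance.** The Design section places the pretest after randomisation, so allocation could in principle influence it. A significance test could not tell that apart from chance, and it still would not identify prognostic variables.

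**Conclusion.** The selection rule should go. That part is firm: it rests on stated text and on 1:1 randomisation, and needs no assumed figure beyond the test level.

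The part on pretest adjustment is conditional. It is stated for H3 and not stated for H1 and H2. If H1 and H2 lack it, the variance of the pre-to-post effect is larger than it need be: the adjusted variance would be 0.65 to 0.90 of the unadjusted over an assumed r of .3 to .8, given equal variances and observed scores. The harm is lost precision, a model that depends on the data, and poor error control under an unnoticed chance imbalance.

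Three stronger readings are not supported. The rule does not inflate overall type I error. The documents do not show that H1 and H2 omit the pretest. And no single gain can be claimed for this trial, such as the equivalent of 120/0.75 = 160 families at r = .5, because the document gives no r. Likewise, the 40% chance of a spurious covariate needs ten independent tests, a count that the article does not give.

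**What to change.** In the Analyses section:

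- Delete the rule that significant baseline differences become covariates, and the tests that feed it. Report baseline characteristics by arm descriptively.
- State that in every H1, H2 and H3 model the change from pretest is regressed on that outcome's own pretest score, regardless of observed imbalance. This includes self-efficacy beliefs.
- For posttest-to-follow-up change, name the pretest as the adjustment variable. The posttest is measured after randomisation and intervention and should not take that role. The gain computed above does not carry over to this contrast.
- Fix any further covariates in advance. Recruitment cohort is one candidate, as the two cohorts are part of the design.

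The cost is one sentence and a few degrees of freedom. The pretest measurements are already planned, and the article states that no participant has yet been recruited, so the change can be made before any data are seen.

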## Materials and methods

### Design

The Parfective Microtrial is a randomized controlled microtrial with a “micro” intervention (i.e., immediate parenting positive feedback) and a control condition that tests physiologically-based differential susceptibility to changes in parenting. Participants are 120 families, with children aged 4–5 years, recruited form a community. Of those families, 60 will be randomly assigned to the “micro” intervention condition and 60 families to the control condition. After enrollment in the microtrial and randomization, the baseline assessment (pretest) will be carried out. The “micro” parenting intervention will be implemented after these baseline assessments. Participants in the care-as-usual control condition receive no immediate positive parenting feedback but will also be taken aside without their child, receiving only the instructions of the experiment. For the intervention condition, we will use an established parental self-efficacy microtrial intervention, which has been found to be effective in fostering parents’ positive parenting (ES = 0.63) and children’s positive behavior (ES = 0.64), by providing *immediate* positive feedback about one’s competence as a parent [10, 11]. Posttest and follow-up assessments will be conducted after 2 weeks and 4 weeks, respectively. The study procedure has been approved by the Ethics Review Board of Tilburg University.

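### Bonferroni is valid here, but Holm's step-down procedure gives the same familywise control and never rejects less: a cheap improvement with a modest gain

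*Protocol article*

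**What the plan says.** The Analyses section states: "The Bonferroni correction is used to reduce chances of obtaining false-positive results (type I errors"). It gives no other reason for the method. It names no step-down procedure, divisor, alpha weighting or simultaneous confidence intervals.

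The correction applies to a plan that tests H1 to H3 on each of these dependent variables: "parental self-efficacy beliefs, parenting behavior, child externalizing behavior and observed parenting and child behavior". That is five. The Hypothesis 1 paragraph counts four: "We have four outcome measurements: reported and observed parenting change and reported and observed change in child behavior". Under Hypothesis 2 there are further tests, because of the way the moderators are handled: "in which each moderator will be tested separately, in separate models".

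On size, the Design section says: "Of those families, 60 will be randomly assigned to the “micro” intervention condition and 60 families to the control condition". The Recruitment section refers to "a priori power analyses for investigating our hypotheses in a two-sided test at α = .05 and power (1-β) = .80" and gives the effect only in words: "Based on previous work that demonstrated medium effects". The Design section reports earlier effects for "positive parenting (ES = 0.63) and children’s positive behavior (ES = 0.64").

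**The concern.** Bonferroni compares every p-value with α/m. Holm makes that comparison only for the smallest p-value and relaxes the threshold for each later one, at the same familywise level. If several outcomes truly respond, Bonferroni therefore holds the second and later ones to a stricter standard than error control requires.

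The point is relevant here because H1 expects change in both parents and children, which is the setting in which a step-down method helps most. The trial also has little power to spare once any correction is applied. What is at stake is efficiency, not validity: some real effects on second and later outcomes may be reported as non-significant without need.

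**Working it through.** **Inputs.** From the protocol article: n = 60 per arm (Design), two-sided α = .05 and power .80 (Recruitment), four outcomes (Hypothesis 1) or five dependent variables (Analyses), and an earlier effect size of 0.63 for parenting (Design). Assumed, because the article gives no figure: d = 0.5 for a medium effect, and correlation 0.3 between outcomes (range 0 to 0.5).

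**The plan's own sample size.** n per arm = 2(1.960 + 0.842)²/d². At d = 0.5 this is 62.8, so 63 per arm and 126 in total (128 with the t distribution). Sixty per arm corresponds to d = 2.802 × √(2/60) = 0.51. Since the planning effect has no number, 120 can be neither confirmed nor refuted. The present point does not depend on it.

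**Power per test, normal approximation.** The test statistic has mean d√(n/2) = 0.5 × √30 = 2.739.
- Unadjusted: Φ(2.739 − 1.960) = 0.78.
- Bonferroni, m = 4, α = 0.0125, critical value 2.498: Φ(2.739 − 2.498) = 0.60.
- Bonferroni, m = 5, α = 0.01: 0.56.

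**Why Holm dominates.** Order the p-values and compare the j-th smallest with α/(m − j + 1), stopping at the first failure. For m = 4 the thresholds are 0.0125, 0.0167, 0.025 and 0.05; Bonferroni uses 0.0125 throughout.
- *Nothing is lost.* If a p-value is at most α/m, so are all smaller ones, and each Holm threshold is at least α/m. Holm cannot stop before reaching it.
- *Same control.* With m₀ true nulls, the first true null that Holm rejects is met at step m − m₀ + 1 or earlier, so its threshold is at most α/m₀. Summing over the m₀ true nulls bounds the familywise error by α, whatever the dependence.
- *Same first step.* The chance of at least one rejection in the family is identical.

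**Size of the gain for H1.** Simulated correlated z statistics, at least 200,000 draws per case, 60 per arm, m = 4, correlation 0.3:

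| Real effects | d | Power per affected outcome, Bonferroni → Holm | All affected outcomes rejected |
|---|---|---|---|
| 4 of 4 | 0.5 | 60% → 69% | 22% → 44% |
| 3 of 4 | 0.5 | 60% → 65% | 29% → 40% |
| 2 of 4 | 0.5 | 59% → 62% (2.3 points) | 40% → 45% |
| 1 of 4 | 0.5 | 59.5% → 59.6% | same as per outcome |
| 4 of 4 | 0.63 | 83% → 91% | 55% → 77% |
| 4 of 4 | 0.3 | 20% → 23% | 1% → 5% |
| 4 of 4 | 0.25 | 13% → 15% | 1% → 2% |

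With all four real at d = 0.5, Holm's power per outcome lies between 0.69 and 0.70 for correlations from 0 to 0.5. With m = 5 and all real, it rises from about 0.56 to between 0.66 and 0.68.

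**Error check.** With no real effect the familywise error is the same for both methods (0.043 to 0.049). With two real effects Holm stays at or below 0.046. In no draw did Bonferroni reject where Holm did not.

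**The case against.** The strongest case against is that nothing in the plan is wrong. Bonferroni controls the error it is meant to control, and a better option does not make it a defect. That stands, and it is why this is an improvement and not an error. A reader might infer that type I error is mishandled or that a conclusion would be false; the documents support neither.

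Second, a reader might take the rise from 60% to 69% as the expected loss. It is the favourable case, with every outcome affected equally. The Introduction itself calls parenting intervention effects small. With all four real at d = 0.25 to 0.3 the gain is only about 2 to 3 points, and with fewer real effects at d = 0.5 it shrinks as the table shows. This objection stands.

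Third, the figures concern H1 main effects, whereas the Abstract and the stated primary aim put moderation by physiology first. Interaction tests at 120 families usually have less power, so Holm would less often get past its first step. H3 concerns change in child behavior only, for which the Secondary outcomes section lists two measures, so there is little to step through. This also stands.

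Fourth, the simulation uses two-group z statistics and not the latent change models planned, so its figures are illustrative. The dominance does not rest on the simulation.

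Fifth, Bonferroni gives simpler simultaneous intervals. That is true, but the article plans none. Finally, Holm needs a defined family; so does Bonferroni, and this does not favor either.

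**Conclusion.** The point holds as a cheap improvement. The article commits to a valid method that is uniformly dominated under the same conditions, and nothing it describes requires the single-step form. That conclusion needs no assumption about effect size or correlation.

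The size of the benefit does need such assumptions, and it is modest: from nearly nothing to about 10 points of power per affected outcome under H1 (m = 4, d = 0.5, correlation 0.3), depending on how many effects are real. For H2 and H3 no figure is claimed.

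A reader might also infer that Holm would restore the planned power of .80. It would not: with four tests at d = 0.5 it reaches 69% at best under the assumptions above, and it does nothing for a power statement that mentions no multiplicity adjustment.

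**What to change.** Replace the Bonferroni sentence in the Analyses section with: *Familywise error is controlled at two-sided .05 by the Holm step-down procedure within each hypothesis's family of tests (the dependent variables, and for H2 the moderators, tested under that hypothesis).* Report Holm-adjusted p-values beside unadjusted 95% confidence intervals.

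The tests in each family should be listed when the change is made, since Analyses names five dependent variables and Hypothesis 1 names four. Bonferroni would need the same list.

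The cost is one sentence, with no added families, visits or measurements. The Trial status section says that no participant has yet been recruited, so the change can be made before any data are seen and registered as the Ethical clearance section provides. The one small downside is that simultaneous confidence intervals matching Holm are less simple than Bonferroni's.
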